f After written informed consent but before study treatment initiation, only SAEs associated with protocol-imposed interventions will be recorded. After study drug initiation, all AEs, SAEs, and pregnancy will be recorded until week 44 or the Early Termination visit. If a subject is discontinued from the study prematurely, AEs and SAEs will be recorded at the Early Termination visit.

g During these contacts, study staff will ask about dose administration and seek information on AEs and SAEs by specific questioning. Information on all AEs and SAEs should be recorded in the subject's medical record and on the AE eCRF.

h Diaries will be completed at week -6 to avoid the potential impact of travel on these outcomes.

i Plasma and serum samples collected and stored for PK and anti-drug antibody studies.

j Buffy coat will only be collected on Week -8, Day 1, and Week +36.

k Week +24 safety labs only if dose was increased at week +16.

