### **10.4 Laboratory Evaluations**

Blood and urine will be collected at the time points described in the Schedule of Events.

Complete blood count with differential (CBCD), liver function tests (LFTs), lipid panel, and basic metabolic panel (BMP) will be performed at Quest Diagnostics or LabCorp at Screening, Week -8, Day 1, Week +2, Week +4, Week +8, Week +12, Week +16, Week +20, Week +24 (only if dose increased at week +16), Week +36, and Week +44. Thyroid function tests (TSH, Free T4) and Quantiferon-TB Gold test will be obtained at Screening.

Anti-anakinra antibodies will not be measured during this pilot study; the rationale for this is based on prior studies showing no effect of anti-anakinra antibodies on pharmacokinetic (PK) parameters, efficacy outcomes or adverse events (AEs) and low incidence of neutralizing anti-anakinra antibodies. However, serum will be collected at Day 1, Week +8, Week +36, and Week +44 and stored for possible future testing of anti-anakinra antibodies if needed for interpretation of safety or efficacy results.

Plasma will be collected and stored for future PK studies at Day 1, Week +8, Week +36, and Week +44.

For post-menarche female patients, a urine pregnancy test will be performed at Screening and at each study visit.

Plasma, serum, urine, and PAXgene tube for RNA will be collected for future biomarker studies at Week -8, Day 1, Week +8, Week +16, Week +36, and Week +44. Consent will be requested to perform these additional biomarker studies on

stored samples in the future as well as genome wide association studies (GWAS) and/or large-scale genomics/transcriptomics assays such as sequencing, methylation and expression.

Buffy coat for DNA will be collected for future biomarker studies at Week -8, Day 1, and Week +36.

Stool will be collected at Week -8, Day 1, Week +8, Week +16, Week +36, and Week +44 for future microbiome studies.

Whole blood will be collected at Week -8, Day 1, Week +8, Week +16, Week +36 and Week +44.

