### ***10.20 Unscheduled Study Visits***

Additional visits will be scheduled with local physicians as needed throughout the study period to address concerning signs or symptoms reported by subjects.

Subjects may withdraw voluntarily from the study at any time. If a subject opts to discontinue, attempts will be made to schedule and conduct an Early Termination visit for medical assessment.

If a subject withdraws after an AE, they will be followed until resolution of the issue or until their condition is stable. In the event that a subject becomes pregnant, then

discontinuation, reporting, and follow-up procedures outlined in Section 13.0 will be followed.

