**13.3 Recording of Adverse Events**

At each contact with the subject, the Investigator must seek information on AEs by specific questioning and, as appropriate, by examination. Information on all AEs should be recorded immediately in the source document, and also in the appropriate AE module of the case report form (CRF). All clearly related signs, symptoms, and abnormal diagnostic procedures results should be recorded in the source document, though should be grouped under 1 diagnosis.

All AEs occurring during the study period must be recorded. The clinical course of each event should be followed until resolution, stabilization, or until it has been determined that the study treatment or participation is not the cause. Serious adverse events that are still

ongoing at the end of the study period must be followed up to determine the final outcome. Any SAE that occurs after the study period and is considered to be possibly related to the study treatment or study participation should be recorded and reported immediately.

Toxicity and AEs will be classified according to the National Cancer Institute (NCI) Common Toxicity Criteria (CTC) V 4.1 and causality will be classified as:

Unrelated - The AE is likely NOT related to study treatment or procedures

Related - The AE is likely related to study treatment or procedures

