## **14.0 Withdrawal of Subjects**

Subjects will be encouraged to complete the study; however, they may voluntarily withdraw at any time. If a subject is withdrawn prior to study completion, attempts will be made to schedule and conduct an Early Termination visit for medical assessment. If a subject cannot be contacted after 5 telephone calls and 3 letters/emails, they will be considered lost to follow-up.

Subjects who discontinue study medication (e.g. due to non-compliance, AEs, etc.) will be asked to remain in the study for follow-up per the study schedule to preserve the ability to perform an intent to-treat (ITT) analysis. If a subject or their legal guardian (as applicable) withdraws consent to participate in the study, attempts will be made to obtain permission to record survival and adverse event (malignancy, hospitalization for infection) data at the Week +44 study point.

Study drug will be discontinued in any subject meeting the following criteria for drug-induced liver injury:

- ☐ ALT or AST > 8x upper limit of normal (ULN)
- ☐ ALT or AST > 5x ULN for more than 2 weeks
- ☐ ALT or AST >3x ULN and (total bilirubin >2x ULN or INR > 1.5)
- ☐ ALT or AST >3x ULN with the appearance of fatigue, nausea, vomiting, right upper quadrant pain or tenderness, fever, rash, and/or eosinophilia (>5%)

Management of suspected drug-induced liver injury will be consistent with the FDA Guidance for Industry Drug-Induced Liver Injury: Premarketing Clinical Evaluation. Specifically, an increase of ALT or AST of >3x ULN will be followed by repeat testing within 48-72 hours of ALT, AST, alkaline phosphatase, and total bilirubin level. There will be inquiry made about symptoms. If symptoms persist or repeat testing shows ALT or AST >3x ULN close observation to determine whether the abnormalities are improving or worsening will be initiated as follows:

- ☐ Repeating liver enzyme and serum bilirubin tests two or three times weekly. Frequency of retesting can decrease to once a week or less if abnormalities stabilize or the trial drug has been discontinued and the subject is asymptomatic.
- ☐ Obtaining a more detailed history of symptoms and prior or concurrent diseases.
- ☐ Obtaining a history of concomitant drug use (including nonprescription medications and herbal and dietary supplement preparations), alcohol use, recreational drug use, and special diets.

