**For example:**

- At week +8, if a subject has not improved in the chosen items then the dose will be increased to 200 mg SC daily.
- At week +8, if a subject has improved, then the dose stays at 100 mg SC daily. However, if this individual then has worsening of the two most bothersome outcomes from week +8 to week +16, after improving from day 1 to week +8, the dose will be increased to 200 mg SC daily at that point (i.e. increase at week +16 after not increasing at week +8).

**Dose will be decreased by 50 mg SC once daily** at any time throughout the study if a participant develops any of the following:

- Neutropenia  $<1200$  cells/microliter persistent for  $\geq 2$  weeks
- Thrombocytopenia  $<50 \times 10^9$  platelets/liter persistent for  $\geq 2$  weeks
- Mild/moderate hypersensitivity reactions including urticaria, rash, and pruritis
- Participants develops a CTCAE grade 3 AE

**Anakinra will be stopped** if the AE above does not resolve within 2 weeks of decreasing the dose by 50 mg SC once daily. Anakinra will be restarted at 0.5 times the last dose administered once the AE is resolved. If the AE recurs with restarting anakinra, it will be discontinued and the subject monitored per protocol.

The starting dose is the same dose level as recommended for adult rheumatoid arthritis patients. The dose escalation is within the range of the recommended dose in Neonatal onset multisystem inflammatory disease (NOMID), including also pediatric patients, is related to body-weight, with a recommended starting dose of 1-2 mg/kg up to a maximum dose of 8 mg/kg.

Smaller children with lower body weight need higher dose levels/kg body-weight in order to achieve similar anakinra serum exposure as in older, heavier children, due to a higher capacity to eliminate anakinra/kg body-weight, based on pharmacokinetic data in 22

systemic-onset juvenile idiopathic arthritis (SJIA) pediatric patients in the age range 2-17 years.

As an example, based on this study, a patient with a body-weight of 20 kg is predicted to require a dose of 4 mg/kg/day to achieve similar anakinra exposure (area under the curve [AUC]0-24h, ss and Cmin, ss) as a dose of 100 mg in a 50 kg patient. Additional examples are given below:

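### After Week +4 the scheduled blood counts are too far apart for the two-week neutrophil and platelet dosing rules, and the protocol neither orders nor times a repeat count

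*Protocol*

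**What the plan says.** Section 27.7 sets a four-step rule for low neutrophils (ANC below 1200 cells/microliter) or low platelets (below 50 x 10^9/L).

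- **Reduce** by 50 mg daily if the low value lasts 2 weeks or more.
- **Stop** if the event "does not resolve within 2 weeks of decreasing the dose by 50 mg SC once daily".
- **Restart**: "Anakinra will be restarted at 0.5 times the last dose administered once the AE is resolved".
- **Discontinue**: "If the AE recurs with restarting anakinra, it will be discontinued and the subject monitored per protocol".

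Section 10.4 schedules the complete blood count with differential (CBCD) at Screening, Week -8, Day 1 and Weeks +2, +4, +8 and +12, and then at "Week +16, Week +20, Week +24 (only if dose increased at week +16), Week +36, and Week +44". Table 1 repeats the condition in footnote k: "Week +24 safety labs only if dose was increased at week +16".

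Two general provisions might supply further counts. Section 10.20 says: "Additional visits will be scheduled with local physicians as needed throughout the study period to address concerning signs or symptoms reported by subjects". Section 13.3 has adverse events followed "until resolution, stabilization, or until it has been determined that the study treatment or participation is not the cause". Neither names a blood count or an interval.

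For liver enzymes, Section 14.0 is explicit. A rise above 3 times the upper limit of normal "will be followed by repeat testing within 48-72 hours of ALT, AST, alkaline phosphatase, and total bilirubin level", with further testing two or three times weekly if it persists.

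**The concern.** The rule runs on two-week clocks and the schedule does not. Followed as written, Sections 10.4 and 27.7 make the reduction and stop decisions late for low counts found after Week +4, and the restart and recurrence checks have no timing at all. The longest interval without a count, Week +20 to Week +36, also applies to subjects raised to 200 mg at Week +8, because the Week +24 draw is limited to those escalated at Week +16.

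Section 15.2 lists neutropenia, thrombocytopenia and serious infection as anakinra risks. A low count may cause no symptoms, and many of these children may be unable to report symptoms they do have, so the symptom-driven visits in Section 10.20 are a weak safeguard. Whether dose actions happen on time depends on testing that the protocol implies but does not state, and practice may differ between subjects.

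**Working it through.** **Inputs.** Count times are from Section 10.4. Windows are from Table 1: ±2 days at Weeks +2, +4, +12, +20 and +24; ±7 days at Weeks +8, +16 and +36. The persistence and stop clocks are 14 days each (Section 27.7).

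**Step 1: gaps between scheduled counts.** Nominal gap = 7 × difference in weeks. Range = nominal gap ± the sum of the two windows. Excess = gap − 14 days.

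| Interval | Nominal gap (days) | Range (days) | Excess over 14 days (range) |
|---|---|---|---|
| +2 to +4 | 14 | 10–18 | 0 (−4 to 4) |
| +4 to +8, +8 to +12, +12 to +16, +16 to +20 | 28 each | 28 ± (2+7) = 19–37 | 14 (5–23) |
| +20 to +24 (only if escalated at +16) | 28 | 28 ± (2+2) = 24–32 | 14 (10–18) |
| +24 to +36 (only if escalated at +16) | 84 | 84 ± (2+7) = 75–93 | 70 (61–79) |
| +20 to +36 (not escalated at +16) | 112 | 112 ± (2+7) = 103–121 | 98 (89–107) |

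After Week +4 the shortest possible on-treatment gap is 19 days, so no scheduled pair meets a 14-day mark. Up to Week +4 the nominal spacing matches the persistence rule. Even so, a low count at Week +2 confirmed at Week +4 has its stop check due at Week +6, and the next count is at Week +8.

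**Step 2: the rule run on scheduled counts only.** The first low count is confirmed at the next scheduled count (reduce). Resolution is judged at the one after (stop check), and restart at the one after that.

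*Not escalated at Week +16 (includes subjects raised to 200 mg at Week +8):*

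| First low | Reduce | Stop check | Restart at the earliest |
|---|---|---|---|
| +4 | +8 | +12 | +16 |
| +8 | +12 | +16 | +20 |
| +12 | +16 | +20 | +36 (treatment over) |
| +16 | +20 | +36 (due +22, 14 weeks late) | none |
| +20 | +36 (due +22, 14 weeks late) | none on treatment | none |

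*Escalated at Week +16:*

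| First low | Reduce | Stop check | Restart at the earliest |
|---|---|---|---|
| +16 | +20 | +24 | +36 (treatment over) |
| +20 | +24 | +36 (due +26, 10 weeks late) | none |
| +24 | +36 (due +26, 10 weeks late) | none on treatment | none |

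In a subject not escalated at Week +16, the stop decision therefore precedes Week +36 only if the first low count is at Week +12 or earlier, and restart only if it is at Week +8 or earlier. After a restart at Week +20, the next scheduled count to detect recurrence is 36 − 20 = 16 weeks later.

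**Step 3: does other text fill the gap?**

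- Section 10.20 depends on reported signs or symptoms.
- Section 13.3 names no test or interval. Under Section 13.2 an abnormal laboratory value is an adverse event only if it meets a listed condition, so a first silent low value may not yet qualify.
- The four-weekly contacts in Table 1 ask about dosing and events but include no draw.
- Section 17.1 covers sharing results, not repeating them.
- The recurrence rule in Section 27.7 refers back to monitoring under the protocol, which is the same sparse schedule.

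None of these orders or times a count.

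**The case against.** The strongest reply is that Section 27.7 is mandatory and applies throughout the study. A rule that turns on persistence or resolution at 2 weeks cannot be carried out without a count at about 2 weeks, so unscheduled counts are implied, and nothing confines the rule to scheduled draws. On that reading the 98-day and 70-day delays require an investigator to see a low count, order nothing for months and fail to apply the rule. This stands as a limit on size: the delays are upper bounds, not expected values. It does not supply a test or a time, and the post-restart check has no implied date at all.

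Other protections are real. Any CTCAE grade 3 event triggers a reduction with no persistence requirement (Section 27.7). Serious infection leads to discontinuation (Section 14.0). Section 13.4 lists grade 3 and grade 4 events among the reasons for terminating the study. Clinically significant results go to the parent and primary care physician (Section 17.1), and an investigator who judges a low count significant makes it an adverse event to be followed (Sections 13.2 and 13.3). The version history also ties the 1200 cut-off to a laboratory reference range, so it is not shown to be a danger level. These points reduce the likely harm.

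This is a single-center pilot of 20 subjects, which limits how far practice will diverge. The liver algorithm follows specific FDA guidance, so its presence does not by itself prove an omission for blood counts. It does show that the protocol specifies timed retesting where it intends it.

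**Conclusion.** The concern holds and should be fixed. After Week +4 the stated schedule cannot support the stated two-week rules on time, and no section orders or times a repeat count. Two consecutive low scheduled counts can show persistence, but late.

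The delay to reduction beyond the two-week mark is 14 days (5 to 23) for a first low count at Weeks +4 to +16. At Week +20 it is 98 days (89 to 107) without escalation at Week +16, or 14 days (10 to 18) with it. At Week +24, after escalation at Week +16, it is 70 days (61 to 79). The stop check can be late by similar amounts, for example 14 weeks for a first low count at Week +16 without escalation.

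These figures assume that no unscheduled count is done, that the count stays low, and that no other safety trigger acts. The protocol gives no frequency of such low counts in this population, so how often this would occur is not estimated.

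**What to change.** State in Sections 27.7 and 10.4, and in a Table 1 footnote, that any on-treatment ANC or platelet value below the Section 27.7 thresholds triggers:

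1. a repeat CBCD at 2 weeks, or sooner if clinically indicated;
2. a CBCD 2 weeks after any dose reduction made for these reasons;
3. CBCDs until resolution is confirmed, before restart;
4. a CBCD about 2 weeks after restart, to detect recurrence.

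The LabCorp or home phlebotomy route in Section 10.26 can be used. The cost is a short amendment and extra venipunctures in affected subjects only: one if the repeat is normal, typically about four for an episode that runs through restart, and more if resolution is slow.

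This covers low counts that have been seen. Whether to add routine counts between Weeks +20 and +36 to find new ones is a separate clinical judgement for the sponsor.

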### **13.4 Study Stopping Rules**

This study may be terminated by the PI, IRB, Safety Monitor or FDA at any time. Reasons for terminating the study may include the following:

- ☐ The incidence or severity of AEs in this or other studies indicates a potential health hazard to subjects.
- ☐ Subject enrollment is unsatisfactory.
- ☐ Data recording is inaccurate or incomplete.
- ☐ Adverse events which may result in study termination include, but are not limited to:
  - Death
  - Cancer
  - Serious infection
  
  - Anaphylaxis
  - Acute hepatic failure
- ☐ ≥ 2 patients develop the same CTCAE Grade 3.
- ☐ 1 patient develops a CTCAE Grade 4 or higher.

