- ☐ Ruling out acute viral hepatitis types A, B, C, D, and E; autoimmune or alcoholic hepatitis; NASH; hypoxic/ischemic hepatopathy; and biliary tract disease.
- ☐ Obtaining a history of exposure to environmental chemical agents.
- ☐ Obtaining additional tests to evaluate liver function, as appropriate (e.g. INR, direct bilirubin).
- ☐ Considering gastroenterology or hepatology consultations.

Study drug will be discontinued in any subject developing one of the following:

- Serious infection (e.g. cellulitis, pneumonia requiring hospitalization, or bone and joint infections, from fungal, mycobacterial and bacterial pathogens; fungal sinusitis)
- Malignancies (e.g. Lymphomas, breast, respiratory, and digestive system cancers)
- Severe hypersensitivity reactions including anaphylactic reactions and angioedema

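### Sections 14.0 and 27.7 order contradictory dose actions for a listed toxicity that is also CTCAE grade 3, and neither says which governs

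*Protocol*

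**What the plan says.** Two sections of the Protocol tell staff what to do with study drug when a child has a toxicity.

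Section 14.0 has two lists. The first opens "Study drug will be discontinued in any subject meeting the following criteria for drug-induced liver injury" and sets transaminase thresholds, for example "ALT or AST > 5x ULN for more than 2 weeks". The second opens "Study drug will be discontinued in any subject developing one of the following" and names serious infection (the entry begins "Serious infection (e.g. cellulitis, pneumonia requiring hospitalization"), malignancy and severe hypersensitivity. Neither list has a reduction step or a restart.

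Section 27.7 orders a 50 mg decrease in the daily dose, at any point in the study, for four triggers: persistent neutropenia, persistent thrombocytopenia, mild or moderate hypersensitivity, and a fourth that reads in full "Participants develops a CTCAE grade 3 AE". If the event is still present two weeks after the decrease, the drug is stopped. Then "Anakinra will be restarted at 0.5 times the last dose administered once the AE is resolved". Discontinuation comes only if the event returns after the restart.

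Footnote e of the Schedule of Events (Section 10.2) refers staff to Section 27.7 for dose decreases and does not mention Section 14.0. Section 13.3 names the NCI toxicity criteria as the grading system; the grade definitions are not reproduced.

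**The concern.** The grade 3 trigger in Section 27.7 has no exception for the events that Section 14.0 lists. A child with, say, a pneumonia that needs admission and is graded 3 therefore falls under two mandatory instructions at once. One ends treatment. The other keeps the child on a lower dose, or stops the drug and later re-exposes the child. The protocol does not say which instruction prevails.

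The stake is mainly safety: whether a child with a serious infection or liver injury stays on, or goes back on, an IL-1 receptor antagonist would depend on which section the staff member opened. It also means that children with the same event could have different exposure from that point up to Week +36, for a reason the protocol does not define.

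**Working it through.** No statistical figure is involved, so the check sets the two rules side by side and works out the dose each one produces.

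| Step | Section 14.0 | Section 27.7 |
|---|---|---|
| Trigger | Named events and liver thresholds, whatever the grade | Any grade 3 event, plus three specific triggers |
| First action | Discontinue | Lower the daily dose by 50 mg and continue |
| Event resolves within 2 weeks of the decrease | Stays off drug | Section 27.7 gives no further step; drug continues at the lower dose |
| Event persists past 2 weeks | Stays off drug | Stop |
| Event then resolves | No restart given | Restart at half the last dose |
| Event recurs after restart | Does not arise | Discontinue |

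**Dose paths under Section 27.7**, taking the last dose given to be the reduced one:

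- From 100 mg: 100 − 50 = 50 mg; if stopped and restarted, 0.5 × 50 = 25 mg.
- From 200 mg: 200 − 50 = 150 mg; if stopped and restarted, 0.5 × 150 = 75 mg. The full 200 mg is reachable only from 200 / 8 = 25 kg upward, because of the 8 mg/kg/day cap.

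Under Section 14.0 the dose for the same event is 0 mg at every step.

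**Can the two be read as one rule?**

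1. The final step in Section 14.0 is discontinuation. Section 27.7 keeps stopping (which a restart can follow) apart from discontinuing (which comes after recurrence). On that usage, discontinuation in 14.0 is most naturally final and is not the first half of a stop-and-restart sequence.
2. Hypersensitivity is divided by severity: mild and moderate in 27.7, severe in 14.0. Serious infection, malignancy and the liver criteria have no such division. The grade 3 trigger also cuts across the hypersensitivity division, since a severe reaction graded 3 would meet it.
3. Neither section refers to the other, and the only pointer, footnote e, leads to 27.7.

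**Where the overlap lies.** It covers events that meet a Section 14.0 entry and are graded 3. A 14.0 event of another grade is outside the grade 3 trigger, and a grade 3 event not listed in 14.0 falls under 27.7 alone. Which events are graded 3 is an assumption, because the grades are not printed. If a transaminase rise above five times the upper limit is graded 3, then a rise lasting more than two weeks means discontinuation under 14.0, but under 27.7 a stop with restart on resolution (taking the decrease to have been made at onset). On the same assumption, a rise above eight times the upper limit means discontinuation at once under 14.0 and a 50 mg decrease under 27.7.

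**The case against.** The best defence is that the plan is tiered: Section 14.0 names the specific stopping events and Section 27.7 deals with the rest. The division of hypersensitivity by severity suggests that this was the intention. It is a reasonable guess at intent, but it is not written, and the unqualified grade 3 trigger together with footnote e points staff the other way. The defence softens the contradiction without removing it.

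Other parts of the defence stand, and they limit what may be concluded. A reader might infer four stronger things that the documents do not support.

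- **That every grade 3 event leads to a restart.** It does not. A restart follows only when the event outlasts the two weeks, the drug is stopped, and the event then resolves. Otherwise the child continues on the lower dose.
- **That any grade 3 liver-enzyme rise meets both rules.** Section 14.0 acts on its own thresholds and accompanying signs, not on grade, and the grades are not in the protocol.
- **That Grade 4 events are part of the same contradiction,** because Section 13.4 lists "1 patient develops a CTCAE Grade 4 or higher" and 27.7 names grade 3. Section 13.4 is a discretionary list for ending the study. Three of the four triggers in 27.7 are not tied to grade 3, and Section 13.0 (item 6) withdraws any subject who cannot safely tolerate participation. At most this is a separate question of completeness.
- **That each affected child moves the intolerability result by 1/20, or 5 percentage points.** Objective 1 in Section 3.0 counts subjects withdrawn for intolerability. Section 14.0 asks those who come off the drug to stay in follow-up, so discontinuing drug is not in itself withdrawal. Section 12.1 bases the primary analyses on everyone who received any treatment, so the conflict removes nobody from them.

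**Conclusion.** Wrong as written: an internal contradiction in a safety rule. For an event that is listed in Section 14.0 and graded 3, one mandatory instruction gives 0 mg with no restart. The other gives continued treatment at 50 mg less, or a stop followed by a restart at half the reduced dose (25 mg from a start of 100 mg, 75 mg from 200 mg). No precedence is stated.

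The conclusion rests on one assumption: that at least some of the events listed in 14.0 can be graded 3 under the criteria named in Section 13.3. How often this would happen among 20 children cannot be estimated from the protocol, and no effect on a primary result is claimed. Which of the two rules is clinically right is not judged here.

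**What to change.** Reconcile Sections 14.0 and 27.7, and footnote e of the Schedule of Events with them. State in both sections:

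1. which section governs when an event meets both;
2. whether the reduction and restart steps of 27.7 can ever apply to an event listed in 14.0.

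Footnote e should then point to both sections. The content of the rule is for the sponsor and its clinicians. The cost is a few sentences of cross-reference in an amendment; no analysis, sample size or visit changes.
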